## Abstract

**Background:**

The treatment of depressive phases of bipolar disorder is challenging. The effects of the commonly used antidepressants in bipolar depression are questionable. Electroconvulsive therapy is generally considered to be the most effective treatment even if there are no randomized controlled trials of electroconvulsive therapy in bipolar depression. The safety of electroconvulsive therapy is well documented, but there are some controversies as to the cognitive side effects. The aim of this study is to compare the effects and side effects of electroconvulsive therapy to pharmacological treatment in treatment resistant bipolar depression. Cognitive changes and quality of life during the treatment will be assessed.

**Methods/Design:**

A prospective, randomised controlled, multi-centre six- week acute treatment trial with seven clinical assessments. Follow up visit at 26 weeks or until remission (max 52 weeks). A neuropsychological test battery designed to be sensitive to changes in cognitive function will be used. Setting: Nine study centres across Norway, all acute psychiatric departments. Sample: n = 132 patients, aged 18 and over, who fulfil criteria for treatment resistant depression in bipolar disorder, Montgomery Åsberg Depression Rating Scale Score of at least 25 at baseline. Intervention: Intervention group: 3 sessions per week for up to 6 weeks, total up to 18 sessions. Control group: algorithm-based pharmacological treatment as usual.

**Discussion:**

This study is the first randomized controlled trial that aims to investigate whether electroconvulsive therapy is better than pharmacological treatment as usual in treatment resistant bipolar depression. Possible long lasting cognitive side effects will be evaluated. The study is investigator initiated, without support from industry.

**Trial registration:**

NCT00664976

## Background

Bipolar disorder (BD) is a psychiatric disorder with a prevalence of 1.7 to 3.7 percent in the adult population [1], characterized by periods of severe affective symptoms with normal periods in between. BD often has an unfavourable outcome [2]. There are two subtypes, Bipolar I and Bipolar II, and depression is arguably a more important facet of both types [3,4]. Depressive episodes are more numerous, last longer, and most suicides occur during these periods [5].

In contrast to the manic phases the treatment options for the depressive phases are poor. Antidepressants have small if any effect in bipolar depression [6], lithium is not very effective [7], there are a few antipsychotics with effect [8,9], but there are some indications for effect of mood stabilizers [10]. The mainstay of current specialist treatment in Norway is a combination of a mood stabilizer, antipsychotic and/or an SSRI or an SNRI. In the last few years the use of the anticonvulsant lamotrigine has become common. Such a combination is in agreement with the recommendations in the treatment guidelines [11]. Electroconvulsive therapy (ECT) was for decades a controversial treatment, but the patients' acceptance of this treatment has increased, leading to an increase in its use [12]. However, ECT resources are limited, and lack of availability often means that it is not a real treatment option. In Norway, the ECT service is fairly good at all regional hospitals. For the most severely ill and treatment resistant BD patients, ECT is considered to be the most effective treatment [11,13]. However, this recommendation is based on clinical experience, as no RCT of ECT in this disorder has been performed. Thus, neither effect size nor comparative efficacy is known [11,14]. This basic lack of knowledge was the motivation for initiating the present study.

No systematic attempts have been made to define what constitutes refractoriness in bipolar depression, and several definitions are used in the literature. In unipolar depression, treatment resistance is present when two or more antidepressive psychopharmacological treatment options have been adequately tried [15]. In the present study with patients suffering from BD, we have used a pragmatic approach and defined refractory bipolar depression as depression that failed to respond to two trials (during lifetime) with antidepressiva and/or mood stabilizer with proven efficacy in bipolar depression (lithium, lamotrigine, quetiapine, olanzapine) in adequate doses for at least 6 weeks or until cessation of treatment due to side effects.

There is little empirical evidence for drug treatment of treatment resistant bipolar depression. Reflecting this, the American Psychiatric Association Treatment Guidelines for BD have a low confidence for their recommendations in this area [11]. The combination of an atypical antipsychotic with documented antidepressant effect and an antidepressant receives the highest grade of recommendation as does ECT.

Patients with BD have specific cognitive impairments affecting a variety of cognitive domains, not only in depressive phases [16-18]. There is little knowledge how cognitive dysfunction changes with treatment of depression. We will use well validated instruments to assess the most important and clinically relevant cognitive domains at baseline and changes during the treatments.

ECT is associated with cognitive side effects [13], but there are few studies comparing cognitive impairment in drug- and ECT-treated patients. The severity, type and duration of the cognitive dysfunction seems to dependent on methods used in ECT administration [19-21]. Given optimal methodology recent studies have found improved global cognitive function as assessed by Modified Mini-Mental State Examination (mMMS) [22] and verbal learning 6 months after completion of an ECT treatment compared to baseline [21]. In the same study, autobiographical memory was impaired at six months after the completion of ECT treatment if ECT was administered by bitemporal electrode placement. Further studies are needed to evaluate possible lasting cognitive side effects of ECT. No studies have evaluated cognitive impairment in patients with bipolar depression treated with pharmacological treatments compared to ECT in a randomised setting.

Health-related quality of life measures have become increasingly important as a type of patient-reported outcome documenting the subjective psychosocial burden associated with chronic illness.

In patients with major depression ECT is widely acknowledged as an effective and appropriate acute treatment. Still questions remain regarding whether ECT is associated with a net improvement in function and quality of life. In recent guidelines from United Kingdom [23] ECT use was restricted until more information becomes available about its effects on memory and quality of life.

A growing body of evidence suggests that inflammation may be linked to depression [24-26]. There are indications that cytokines may cause depressive episodes [27]. Few studies have investigated the immune system in BD. One study found that BD is associated with increased production of the pro-inflammatory cytokines, both in the manic and depressed phase (IL-8 and TNF-α) compared to healthy subjects [28].

Two recent reviews [29,30] concluded that inflammation appears relevant to BD across several important domains and proposed that TNF-alpha modulation is a target for disease-modifying treatment of BD. Further research is warranted to investigate the reciprocal associations between inflammation and symptoms, comorbidities, and treatments in BD.

The aim of the current study is to document the effect size, relative effect size and adverse effects of ECT compared to treatment as usual in treatment resistant bipolar depression. We want to assess the cognitive function in bipolar depression, and how ECT and treatment as usual affect cognitive functioning. Furthermore possible inflammation processes involved in bipolar depression will be investigated. The design enables us to assess changes in a wider spectrum of cytokines as a function of treatment modality and changes in clinical status.

## Methods

### Study design

This trial is a randomised controlled multi-centre study aimed to study efficacy and cognitive side effects of ECT for the treatment of treatment resistant depression in BD, compared to combined pharmacological treatment, including the MAOIs tranylcypromine and phenelzine. A flow chart of the study design is shown in Fig. 1.

**Figure 1 F1:**
[figure not shown]
**Flow Chart of Study Design**.

Relevant patients with depression are addressed in order to establish whether they are willing to be screened for the study. The patients must be assigned a patient number and sign the consent form after receiving oral and written information about the study prior to undergoing any study procedures.

Each treatment trial lasts 6 weeks. The medication that would be used if a patient should be randomized to drug treatment will be determined at enrolment, before randomisation. If a patient receives ECT and reaches remission earlier than six weeks, the ECT treatment is terminated and the patient is switched to maintenance therapy. If a patient or the treating clinician decides that the patient could receive better treatment outside of the study, the patient may leave the study at all times, as specified in the informed consent. In case of remission after the six weeks trial the patient continues with maintenance drug treatment at the clinicians decision, guided by relevant algorithm as for example in Goodwin & Jamison 2007 [31]. In case of non- remission the clinician might consider the other treatment condition. This will not be part of the present study.

### Subjects

#### Trial sample and recruiting centres

132 patients fulfilling the criteria below will be included into this study by nine centres in Norway.

All the patients will first be included in the "Bipolar Research And Innovation Network, Norway" (BRAIN) study, a multicenter study describing bipolar disorder patients in Norway. This study is approved by The Regional Committee for Medical and Health Research Ethics, Middle - Norway. The patients will give written informed consent both to the BRAIN study and the ECT-study.

#### Inclusion and exclusion criteria

The inclusion criteria were designed to ensure that the included patients are typical for patients referred to ECT in Norway in order to have results that are clinically significant, while the exclusion criteria are designed to ensure the patients' safety. Inclusion and exclusion criteria are shown in table 1 and 2.

**Table 1 T1:** Inclusion criteria

Diagnosis of DSM-IV-TR [52] of Bipolar I or Bipolar II disorder as verified by the semi-structured diagnostic interviews SCID [37] or MINI plus [36]. The diagnosis may be supported by information from significant others, and from hospital records. Angst's hypomania checklist [53] is used to increase the detection of hypomanic symptoms. SCID or MINI plus will be used to diagnose the patient.
ECT is indicated.
Severity: meet DSM-IV-TR criteria of depressive episode, MADRS [40] of 25 or above
Treatment resistance: None response to two trials (during lifetime) with mood stabilizers with proven efficacy in bipolar depression (lithium, lamotrigine, quetiapine, olanzapine) and/or antidepressants.
A trial is defined as at least 6 weeks in adequate or tolerated dose as reported by the patient, or patients that have been unable to comply with 6 weeks trials of mood stabilizer or an antidepressant.
None response: Less than 50% reduction in MADRS values or still meet DSM -IV-TR criteria of depressive episode
Inpatients the first week after start of treatment condition
The patients are to be treated by the psychiatrist at the hospital for the whole duration of the study (6 weeks)
Age ≥ 18
Patient competent to give informed consent according to the judgement of the clinician
Written informed consent
Patient sufficiently fluent in Norwegian language to ensure valid responses to psychometric testing (for patients enrolled to neuropsychological assessment: Norwegian as primary language or 12 years attendance of a Norwegian school)

**Table 2 T2:** Exclusion Criteria

Earlier ECT none response
ECT within the last six months
Rapid cycling BD (e.g.4 or more episodes per year)
Use of medication or substances (such as pethidine, alcohol, drugs) incompatible with treatment (medication or ECT). Such medication must be stopped a least 5 half-lives before start of treatment.
Current use of all other psychotropic medication during the study period with the exception of the following: The use of alimemazine (max dose 30 mg daily), chlorpromazine (max dose 25 mg × 2 daily) and chlorprothixene (max dose 20 mg × 2) is allowed. The use of mianserine (max dose 10 mg daily) is allowed. Medication related to the ECT procedure is allowed.
For Medication in control group refer to Medication in control group - Treatment As Usual
Inability to comply with study protocol
Unstable serious medical conditions, including clinically relevant laboratory abnormalities
Conditions that affect neuropsychological assessment such as Parkinson's Disease, Multiple sclerosis, stroke, alcohol and substance abuse or dependence (according to SCID or DSM-IV-TR)
Fertile women without adequate contraception (Adequate contraception includes: abstinence, oral contraceptives, intrauterine devices, barrier method)
Young Mania Rating Scale (YMRS) [43] of 20 or more
Patient at high suicidal risk according to clinicians' judgement

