### Inclusion, randomization and masking of study groups

All patients suffering from a major depressive episode admitted to one of the nine study centres are evaluated for inclusion. During the screening the local participating psychiatrist will determine whether the patient fulfils the inclusion criteria and none of the exclusion criteria. Patients will be randomly assigned to the two groups. The randomization is stratified separately in each study centre. The patient and treating psychiatrist are unmasked about treatment modality. The assessments of depressive symptoms before and after ECT will be audio-taped. The audio-tapes will be co-rated by trained study personnel who are not involved in the treatment of the study patients. The analyses will be preformed on audio taped scores. There might be some patients who do not accept audio taping, in these cases investigator-rating will be used. Neuropsychological assessment is performed by trained test assistants who are blinded about treatment modality.

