### Description of treatment

#### Method of assigning patients to treatment groups/Randomization

Patients' eligibility will be established before randomization to one of the treatment options. Relevant patients with BD are addressed in order to establish whether they are willing to be screened for the study. The patients must be assigned a patient number and sign the consent form after receiving oral and written information about the study prior to undergoing any study procedures. Patients will be randomized strictly sequentially, as patients are eligible for randomization. If a patient discontinues from the study, the patient number will not be reused, and the patient will not be allowed to re-enter the study.

We perform a stratified randomization separately for each centre using the default random number generator of SPSS 15 with a random seed. The randomization lists are kept concealed from the investigators.

After randomization patients will enter a wash out phase if necessary. The recommended time for patients to be without concomitant medication in contradiction to the study protocol is 5 t 1/2 for patients randomized to ECT and a varying time for patients randomized to treatment as usual.

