#### Procedures in case of pregnancy

Pregnancy itself is not regarded as an AE unless there is a suspicion that the study medicine may have interfered with the effectiveness of a contraceptive medication. However, the outcome of all pregnancies (spontaneous miscarriage, elective termination, normal birth or congenital abnormality) must be followed up and documented even if the patient was discontinued from the study.

All reports of congenital abnormalities/birth defects are SAEs. Spontaneous miscarriages should also be reported and handles as SAEs. Elective abortions without complications should not be handled as AEs. All outcomes of pregnancy must be reported to the principal investigator.

Female patients of childbearing potential must be using a reliable method of contraception. Reliable methods of contraception include hormonal contraceptives (e.g. oral contraceptives or long term injectable or implantable hormonal contraceptive), double-barrier methods (e.g. condom and diaphragm, condom and foam, condom and sponge), intrauterine devices and tubal ligation. Female patients must have a negative urine human chorionic gonadotropin (HCG) test at enrolment.

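### Table 2 accepts any barrier method as adequate contraception, while the mandatory rule in the pregnancy section names only double-barrier methods among the barrier options

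*Protocol article*

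**What the plan says.** The protocol article states the contraception requirement twice.

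- **Inclusion and exclusion criteria, Table 2.** The excluded group is "Fertile women without adequate contraception (Adequate contraception includes: abstinence, oral contraceptives, intrauterine devices, barrier method". The barrier entry carries no qualifier.
- **Procedures in case of pregnancy.** The rule is mandatory: "Female patients of childbearing potential must be using a reliable method of contraception". The methods follow: "Reliable methods of contraception include hormonal contraceptives (e.g. oral contraceptives or long term injectable or implantable hormonal contraceptive), double-barrier methods". The list then gives paired examples and ends: "double-barrier methods (e.g. condom and diaphragm, condom and foam, condom and sponge), intrauterine devices and tubal ligation". The same paragraph requires a negative pregnancy test at enrolment, so it addresses entry as well as the handling of pregnancies that occur later.

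Three other places show how Table 2 is used. The article says that "the exclusion criteria are designed to ensure the patients' safety". At screening, "the local participating psychiatrist will determine whether the patient fulfils the inclusion criteria and none of the exclusion criteria", and "eligibility will be established before randomization to one of the treatment options". Under Withdrawal criteria, meeting an exclusion criterion is a ground for taking the patient out of the study.

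**The concern.** One requirement is set at two levels of strictness, and nothing in the article says which prevails or that one applies at entry and the other later. The looser version sits in the table that the local psychiatrist uses as the screen. The stricter one sits among the adverse event procedures, where someone deciding eligibility is less likely to look.

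What is at stake is safety. Table 1 requires inpatient status only for the first week of a six-week treatment phase, so contraception is a practical matter during the trial. The article treats fetal harm as serious: "All reports of congenital abnormalities/birth defects are SAEs". If the authors judged two barriers to be necessary, the eligibility table does not carry that judgement to the people who apply it.

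**Working it through.** No arithmetic in the plan bears on this point, and there is no stated figure to reproduce. The check is a comparison of the two lists.

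| Method | Table 2 | Procedures in case of pregnancy |
|---|---|---|
| Abstinence | named | not named |
| Oral contraceptives | named | named |
| Injectable or implantable hormonal | not named | named |
| Intrauterine device | named | named |
| Barrier | named, unqualified | named only as double-barrier |
| Tubal ligation | not named | named |

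**Step 1: sort the Table 2 methods.** Table 2 names 4 methods. Of these, 2 reappear in the pregnancy section (oral contraceptives, intrauterine devices), 1 reappears only in a stricter form (barrier), and 1 does not reappear (abstinence): 2 + 1 + 1 = 4.

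**Step 2: separate a real difference from a difference in listing.** Both lists are introduced by a form of the word include, so neither is exhaustive. A method present in one and absent from the other is therefore not in itself a conflict. That disposes of abstinence, injectables, implants and tubal ligation. The barrier entry is of another kind: both lists contain it, and one narrows it. All 3 examples in the pregnancy section (condom with diaphragm, with foam, with sponge) combine two items, and 0 of 3 is a single barrier. If one barrier sufficed, the word double would do no work.

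**Step 3: apply both texts to one case.** Take a fertile woman who uses a condom alone.

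- At entry, Table 2 counts a barrier method as adequate, so she is not excluded. She uses no method that the pregnancy section names as reliable.
- During treatment, suppose she moves from oral contraceptives to a condom alone. By Table 2 she still meets no exclusion criterion, so that ground for withdrawal does not arise. By the pregnancy section she has left the named methods.

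The two texts can therefore give different answers for the same woman, both at entry and while she is on study.

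**The case against.** The strongest reply is that the two texts can be read together. Table 2 offers a generic label in a one-line entry, the pregnancy section gives the detail, and a specific mandatory rule ordinarily governs shorthand. That rule covers all women of childbearing potential, with no exception for those who passed Table 2, and Table 2 itself excludes patients unable to comply with the protocol. An article also condenses, and the full protocol's criterion may already say double-barrier.

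Part of this stands. A centre that reads the whole document and lets the stricter text prevail will reach the safer result, and what the nine centres were actually given cannot be seen. But the article states no order of precedence, and condensation excuses missing detail, not two printed rules of different strictness.

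Three stronger readings are tempting and are not supported:

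- A reader might infer that centres would classify the same woman differently as a protocol deviation. The relevant category under Protocol Deviations concerns the entry criteria, and the article places these in Tables 1 and 2. Table 2 therefore governs that category, and the split does not follow.
- A reader might infer that the pregnancy section forbids a single barrier. It does not say so; its list is open, and it only fails to name one.
- A reader might infer that pregnancy protection at entry is generally lacking. A negative urine test at enrolment is mandatory and is scheduled at visit 1 in Table 4.

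**Conclusion.** The point holds as a minor inconsistency in eligibility and safety wording. Table 2 lets a screener admit, and under Withdrawal criteria retain, a woman using a single barrier, which the mandatory rule does not name as reliable.

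The conclusion rests on two readings: that an unqualified barrier method covers a single barrier, and that double with paired examples is meant as a restriction. Both are the ordinary sense of the words. How many women would be affected cannot be derived from the document, and no increase in pregnancy risk is shown. Sample size, power and the primary analysis are unaffected.

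**What to change.** In Table 2, replace barrier method with double-barrier method. Then use one list in both places: abstinence (which Table 2 already accepts), hormonal contraceptives including oral, long-term injectable and implantable forms, double-barrier methods, intrauterine devices, and tubal ligation.

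This is a wording amendment. Its downside is that a few women relying on a single barrier would have to change method or not enter. No recalculation or change to the analysis is needed.
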